### Outcome assessments

All patients will be followed up by trained neurologists blinded to study data. The primary and secondary endpoints of this study are summarized in Table 2. The SE-GRACE trial is designed with combination of clinical, imaging and biochemical outcomes to provide information about clinical benefits and relevant mechanism of action. Subjects will be followed up in person or through telephone review at 30 ± 7 days, 90 ± 14 days (the primary end-point), 180 ± 30 days and 360 ± 30 days after the onset of AIS, using modified Rankin Scale (mRS), Barthel Index (BI) and Informant Questionnaire on Cognitive Decline in the Elderly (IQCODE) (Fig. 1) [21, 22]. The primary outcome will compare the proportion of “good outcome” in the glibenclamide-treated group to the placebo group, with good outcome defined as a patient with a mRS of 0–2 at 90 days after the onset. The BI is a 10-item measure of activities of daily living which is frequently used in clinical practice and as a trial outcome measure in stroke, with a total score of 60 to 100 generally regarded as good outcome [23]. The IQCODE is an informant-based assessment tool for diagnosis of poststroke dementia and/or multidomain cognitive impairment, with a pooled sensitivity of 0.81 and specificity of 0.83 in a recent a systematic review [22]. The cutoff value of IQCODE for diagnosing poststroke dementia is generally considered to be > 3.4 [21, 22].

**Table 2 Tab2:** Primary and secondary endpoints of the trial

Outcome	Description
Primary outcome	The ratio of mRS ≤ 2 at 90 days after the stroke onset
Secondary outcome	1. The ratio of NIHSS decreased ≥4 points at 7 days after the stroke onset
	2. The ratio of parenchymal hemorrhagic transformation in cranial CT within 96 h after the onset
	3. The ratio of midline shift ≥6 mm in cranial CT within 96 h after the onset
	4. The mRS shift at 90 days after the onset
	5. The ratio of Barthel Index of 60–100 points at 90 days after the onset
	6. The proportion of Informant Questionnaire on Cognitive Decline in the Elderly (IQCODE) of ≤3.40 at 6 months and 1 year after the stroke onset
	7. The serum concentration of MMP-9 at baseline, and at 24, 48, and 72 h after onset
Safety outcome	1. The mortality at 90 days after the onset
	2. The ratio of neurological deterioration (NIHSS increased ≥4 points) within 24 h after the onset
	3. The incidence of hypoglycemia (random blood glucose < 3.9 mmol/L)

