### Sample size estimation

The sample size calculation was based on previous findings, and the proportion of patient with a mRS of 0–2 at 90 days of 41% was estimated for the placebo group, and of 58% was assumed for the glibenclamide-treated group [11]. When half of the planned subjects finish their 90-day follow up an interim analysis will be conducted and the O’Brien - Fleming method will be used to control the type I error. Using nQuery + nTerim 4.0 (Statistical Solutions Ltd., Farmer’s Cross, Cork, Ireland) with a 2-sided χ^2^ test, a two-sided significance level of 0.05, a power of 80%, the O’Brien - Fleming alpha spending function and a dropout rate < 10%, 153 patients are required in each group, for a total sample size of 306.

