### Statistical analyses

The primary outcome will be compared between 2 groups using χ^2^ tests, and the confidence interval of the rate difference will be calculated using the Newcombe’s method [27]. Common risk difference for multiway 2 × 2 tables stratified by endovascular treatment and baseline NIHSS score (≥ 14 or < 14) will also be reported. The Mantel-Haenszel estimate, confidence limits, and test for the common risk differences by using Mantel-Haenszel stratum weights and the Sato variance estimator will be used. When half of the planned subjects are recruited and their 90-day follow up are finished, interim analysis will be conducted by a selected biostatistician. O’Brien - Fleming method will be used to control the Type I error. The trial will be stopped early when the primary outcome of the interim analysis significantly favors or contradicts the usage of glibenclamide.

For baseline variables and other outcomes, comparisons between normally distributed continuous variables, expressed as mean ± SD, will be performed using 2-sample t tests; non-normally distributed continuous variables, presented as median and interquartile range, will be analyzed using Wilcoxon rank sum tests. Pearson χ^2^ or Fisher exact tests will be used, as appropriate, for categorical data, which will be expressed as percentages. For secondary outcomes mRS shift and MMP-9, mixed effect model will also be used.

For safety analysis, all adverse events and serious adverse events, including deaths, will be summarized by body systems in terms of frequency, severity, and relatedness to the study drug using the MedDRA codes. Frequencies of adverse events from these two groups will be reported. Pearson χ^2^ or Fisher exact tests will be used, as appropriate, to compare the incidence of adverse events between the two groups.

Subgroups analyses will be performed according to pre-defined design variables, such as: sex, age (≤ 60 years vs. 61–74 years), endovascular treatment, NIHSS grade (4–13 vs. 14–25), time window in rtPA thrombolysis (< 3.5 h vs. 3.5–4.5 h), and study drug treatment time (< 6 h vs. 6–10 h).

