The primary and secondary end points will be analyzed based on the modified intention-to-treat (mITT) population which excludes those patients who do not receive treatment or control and has no efficacy outcome data, and those subjects who are diagnosed with posterior circulation occlusion alone after being included. Per-protocol patients who finish the treatment protocol with good compliance, will also be analyzed as a sensitive analysis. Safety analyses will be done in patients receiving allocated treatment. Last observation carried forward method will be used to deal with the missing data of primary outcome, and multiple imputation method will also be used as sensitive analysis. All analyses will be 2-tailed and a significance level of 0.05 will be used for all outcomes. All data analyses will be performed using SAS version 9.4 (SAS Institute, Cary, NC).

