Based on the above data and as a complement to the GAMES-RP study, we conducted this prospective, randomized, double-blind, placebo-controlled, multicenter trial to evaluate the efficacy of glibenclamide in AIS patients treated with intravenous rtPA. Although parenteral glibenclamide had been used in animal studies and the GAMES-RP study (RP-1127), no commercial formulation for clinical use is available in China, so the enteral route was chosen. Glibenclamide is well absorbed from the gastrointestinal tract with its peak plasma concentration occurred 1.5–2 h after ingestion and has a duration of action approximately for 18 h [36]. Besides, oral glibenclamide has been safely used for decades, with limited evidence regarding safety issues, except hypoglycemia [37]. Since its apparent potency may increase at the acidic microenvironment found in ischemic brain [7], a relatively low-dose regimen of glibenclamide would be reasonable and thereby the risk of hypoglycemia will be greatly reduced [15]. Given that poststroke hyperglycemia is common and prolonged in nondiabetic as well as diabetic patients, our low-dose regimen of glibenclamide, which is about 25% of its regular dose for treating diabetes, might not substantially increase the risk of hypoglycemia in the study population. In our preliminary study, only one episode of hypoglycemia was recorded during treatment with the glibenclamide in the nondiabetics (*n* = 15), whereas there was 8 episodes of hypoglycemia in the controlled nondiabetics (*n* = 145) (post-hoc analysis) [17]. The low risk of hypoglycemia in these patients may also be related to our early initiation of nutritional support. Therefore, in the SE-GRACE study, early nutrition support and blood glucose monitoring will be adopted to minimize the risk of hypoglycemia. Because the price of oral glibenclamide is very low, a large number of patients would benefit from this agent if it gets proved to be effective.

In conclusion, this article describes the design and planned analysis used in the SE-GRACE trial for the first publication of the primary outcomes. This approach minimizes the overall risk of bias and data-driven results.

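### The 0.05 level is applied to every outcome, and the seven secondary outcomes are not ranked, gated on the primary or labelled exploratory

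*Protocol article*

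**What the plan says.** There is one primary outcome, the proportion with mRS 0–2 at 90 days. It is powered at "a two-sided significance level of 0.05, a power of 80"%, with one interim look at half the patients and O'Brien–Fleming control of the type I error (Sample size estimation; Statistical analyses).

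For the level of all other tests, the last paragraph of Statistical analyses states: "All analyses will be 2-tailed and a significance level of 0.05 will be used for all outcomes".

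Table 2 lists seven secondary outcomes: NIHSS improvement at day 7, parenchymal haemorrhage on CT, midline shift on CT, mRS shift at 90 days, Barthel Index at 90 days, IQCODE and serum MMP-9. Two of them have several time points. IQCODE is defined as "The proportion of Informant Questionnaire on Cognitive Decline in the Elderly (IQCODE) of ≤3.40 at 6 months and 1 year after the stroke onset", and MMP-9 is measured at baseline and at 24, 48 and 72 h. Two are analysed in a second way: "For secondary outcomes mRS shift and MMP-9, mixed effect model will also be used". The article does not say which result governs.

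Outcome assessments describes the trial as "designed with combination of clinical, imaging and biochemical outcomes to provide information about clinical benefits and relevant mechanism of action". It does not say which outcomes serve which purpose.

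The subgroup paragraph begins "Subgroups analyses will be performed according to pre-defined design variables, such as" and then names six variables. It gives no subgroup test, significance level or interaction analysis.

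**The concern.** The article does more than leave multiplicity to a later document. It fixes a level, the same for every outcome, and attaches no condition to it. Followed as written, the rule lets a nominally significant Barthel, midline-shift, haemorrhage, IQCODE or MMP-9 result be declared significant at the same threshold as mRS 0–2, even when mRS 0–2 has failed. The report could then present the most favourable of several secondary results as a finding, and nothing in the plan would mark it as weaker evidence than the primary.

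The subgroup list has a related fault. Its variables are described as pre-defined, but the words that introduce them leave the list open, so a variable chosen after seeing the data could be added without departing from the text.

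**Working it through.** **Inputs.** Level 0.05, two-sided, for every outcome (Statistical analyses). Seven secondary outcomes (Table 2). Time points: IQCODE two, MMP-9 three after baseline (Table 2). The article gives no correlation between outcomes, so a range is assumed.

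**The plan's own figure.** The article states no family-wise error rate for the secondary outcomes. Its sample size shows what the 0.05 was set for. The rates are "41% was estimated for the placebo group, and of 58% was assumed for the glibenclamide-treated group". The pooled two-proportion formula without continuity correction is

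n = [1.96·√(2p̄q̄) + 0.8416·√(p₁q₁ + p₂q₂)]² / (p₁ − p₂)², with p̄ = 0.495

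= [1.96·√0.49995 + 0.8416·√0.4855]² / 0.17² ≈ 134.6, so 135 per group.

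The O'Brien–Fleming spending function with two looks multiplies this by 1.0037, giving 135.5, so 136. Allowing 10% dropout gives 136/0.9 = 151.1, so 152, against the stated 153. The design therefore reproduces to within one patient per group. The whole 0.05 is spent on the primary outcome over two looks.

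**Number of tests.** One test per listed outcome gives 7. Testing each time point gives 5 single-time outcomes + 2 (IQCODE) + 3 (MMP-9) = 10. Seven is the documented number of outcomes. Ten is an upper reading, because a mixed model for MMP-9 could give a single comparison.

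**Chance of at least one p<0.05 under no effect, independent tests:** 1 − 0.95^k.
- k = 7: 1 − 0.698 = 30.2%.
- k = 10: 1 − 0.599 = 40.1%.
- The chance passes 50% only when k > ln 0.5 / ln 0.95 = 13.5, that is from 14 tests.

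**Correlated tests.** Test statistics were simulated as Z_i = √ρ·C + √(1−ρ)·E_i, with C and E_i standard normal, in 400,000 sets. A set counts if any |Z_i| > 1.96.

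| Assumed ρ | 7 tests | 10 tests |
|---|---|---|
| 0 | 30.1% | 40.1% |
| 0.3 | 27.1% | 35.2% |
| 0.5 | 22.9% | 28.7% |
| 0.7 | 17.8% | 21.3% |
| 0.8 | 15.1% | 17.3% |

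An uneven structure for ten tests gives 32.5%, inside the same range. It assumes 0.6 among the five clinical-scale tests and among the three MMP-9 tests, 0.3 between the two CT outcomes and 0.2 elsewhere.

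**Direction.** Counting only false positives in favour of glibenclamide (0.025 per test, independent), the chance is 1 − 0.975⁷ = 16.2% for seven tests and 1 − 0.975¹⁰ = 22.4% for ten.

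**After the fix.** If a secondary sequence opens only after a significant primary, then under no effect on any outcome a false secondary claim requires a false primary result first, so its chance is at most 5%. With an exploratory label no secondary claim is made, and no error rate has to be held.

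**The case against.** The strongest reply is that 0.05 is a per-test level and the article never promises 5% across the secondary outcomes. A fixed sequence would itself test each step at 0.05, so a SAP could add a gate or an exploratory label without contradicting the sentence. The outcomes are called secondary, they are all listed in advance, and some plainly serve the mechanistic aim. Much of this stands: the rule is incomplete rather than arithmetically wrong, and a ratio of the family-wise chance to 0.05 would compare two different quantities. It does not remove the point. The sentence as published permits a claim on any outcome whatever the primary shows, and the article nowhere withholds that permission.

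A reader might infer more than the article supports:

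- *That a chance positive is likely.* For the secondary outcomes alone, none of the figures above reaches 50%.
- *That there are definitely ten tests.* This assumes separate MMP-9 tests at each time point, although a mixed model is also planned.
- *That both levels of all six subgroup variables are tested at 0.05.* The sentence speaks of outcomes, and the subgroup paragraph gives neither a test nor a level. A subgroup error rate would rest on tests that the article does not state, so none is given here. The open list is a fault regardless.
- *That the closing claim of the Discussion, "This approach minimizes the overall risk of bias and data-driven results", is broken by this rule.* It follows a sentence about describing the plan for the first publication of the primary outcomes, and most naturally refers to publishing that plan in advance.

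**Conclusion.** The point holds for the secondary outcomes. Under no effect, about 23% of such trials would give at least one nominally significant secondary result, taking seven tests and a correlation of 0.5. The range is 15% (correlation 0.8) to 30% (independence). Testing IQCODE and MMP-9 at each time point raises the upper end to 40%. The correlations are assumptions, and equal correlation between all pairs is a simplification.

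The primary conclusion is not in question: there is one outcome, with O'Brien–Fleming control over both looks. Read literally, the sentence would put the final primary test at 0.05 rather than at about 0.049, for an overall level of about 0.051. That difference is negligible, and the same section names the O'Brien–Fleming method for this test.

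The weakness lies in what may be claimed from the secondary outcomes, above all when the primary is not significant. It should be corrected before results are known.

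**What to change.** In the last paragraph of Statistical analyses, limit the significance-level sentence to the primary outcome, at its O'Brien–Fleming final level. Then choose one of two rules for the secondary outcomes in Table 2:

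1. Label them all exploratory and report estimates with 95% confidence intervals and nominal p-values that support no efficacy claim.
2. Test a short prespecified sequence, chosen by the sponsor, only if the primary is significant, and label the remaining secondary outcomes exploratory.

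In the subgroup paragraph, remove the open-ended wording so that the six named variables form a closed list. State that each is judged by a treatment-by-subgroup interaction, and label the results exploratory.

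The change is to wording here and in the SAP, with no extra patients or data. The small price is that an isolated secondary or subgroup p<0.05 can no longer be presented as a significant finding.

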### Patient and public involvement

There was no patient or public involvement in the study design.

## Discussion

Intravenous rtPA thrombolysis is still the mainstay of AIS treatment. However, the restricted time window and hemorrhagic transformation related side effects have limited its wide application. Even in patients treated with intravenous rtPA, more than 50% of them continue to have substantial disability [28]. Moreover, thrombolytic therapy substantially increases the risk of hemorrhagic transformation after AIS, probably by disrupting the blood-brain barrier. Researchers have tried to enhance the efficacy of intravenous rtPA thrombolysis by add-on therapy [29, 30], and some benefits have been observed from the selective population [31].

Glibenclamide is a second generation sulfonylurea that has long been used for treating type 2 diabetes mellitus. By directly binding to the sulfonylurea receptor 1 (SUR1) subunits of K-ATP channels, glibenclamide causes the channel closure and results in membrane depolarization in the pancreatic β-cell leading to increased insulin secretion [32]. During the last decade, glibenclamide has repeatedly shown to exert prominent neuroprotection via blocking of the newly synthesized SUR1-transient receptor potential M4 (SUR1-TRPM4) channel [33]. In a rodent model of transient middle cerebral artery occlusion, glibenclamide reduced cerebral edema, infarct volume and mortality by 50% [7]. Findings from other rat models of ischemic stroke and data from independent laboratory further support the significance of glibenclamide in alleviating ischemic injury [8, 34]. Strikingly, glibenclamide attenuated rtPA-related brain injury, with a therapeutic time window of 10 h [13].

A retrospective study in AIS patients with type 2 diabetes mellitus who took sulfonylurea agents both at the time of stroke and during hospitalization had got better outcome than those who did not [10]. Another study reported sulfonylurea agents were associated with less hemorrhagic transformation, indicating that sulfonylurea might function in blood-brain barrier protection [11]. Postmortem examination using specimen from patients with brain infarction supports the notion that sulfonylurea takes effect by blocking the upregulated SUR1 [35].

A double-blind, randomized, placebo-controlled phase 2 trial has been conducted to test the efficacy of intravenous glibenclamide (RP-1127) in preventing brain swelling after large hemispheric infarction (GAMES-RP) [15]. Patients (aged 18–80 years) with a clinical diagnosis of large anterior circulation hemispheric infarction for less than 10 h and baseline diffusion-weighted MRI image lesion volume of 82–300 cm^3^ on MRI were enrolled. Although the study was suspended for funding reason, interim results revealed that glibenclamide was well tolerated and reduced 30-day mortality as well as midline shift [12]. Moreover, glibenclamide decreased the serum concentration of MMP-9, indicating a protective role of glibenclamide in blood-brain barrier. In our preliminary study, we found that a low-dose regimen of oral glibenclamide was well tolerated and was associated with reduced brain edema and consequential severe disability and death [17].

Based on the above data and as a complement to the GAMES-RP study, we conducted this prospective, randomized, double-blind, placebo-controlled, multicenter trial to evaluate the efficacy of glibenclamide in AIS patients treated with intravenous rtPA. Although parenteral glibenclamide had been used in animal studies and the GAMES-RP study (RP-1127), no commercial formulation for clinical use is available in China, so the enteral route was chosen. Glibenclamide is well absorbed from the gastrointestinal tract with its peak plasma concentration occurred 1.5–2 h after ingestion and has a duration of action approximately for 18 h [36]. Besides, oral glibenclamide has been safely used for decades, with limited evidence regarding safety issues, except hypoglycemia [37]. Since its apparent potency may increase at the acidic microenvironment found in ischemic brain [7], a relatively low-dose regimen of glibenclamide would be reasonable and thereby the risk of hypoglycemia will be greatly reduced [15]. Given that poststroke hyperglycemia is common and prolonged in nondiabetic as well as diabetic patients, our low-dose regimen of glibenclamide, which is about 25% of its regular dose for treating diabetes, might not substantially increase the risk of hypoglycemia in the study population. In our preliminary study, only one episode of hypoglycemia was recorded during treatment with the glibenclamide in the nondiabetics (*n* = 15), whereas there was 8 episodes of hypoglycemia in the controlled nondiabetics (*n* = 145) (post-hoc analysis) [17]. The low risk of hypoglycemia in these patients may also be related to our early initiation of nutritional support. Therefore, in the SE-GRACE study, early nutrition support and blood glucose monitoring will be adopted to minimize the risk of hypoglycemia. Because the price of oral glibenclamide is very low, a large number of patients would benefit from this agent if it gets proved to be effective.

In conclusion, this article describes the design and planned analysis used in the SE-GRACE trial for the first publication of the primary outcomes. This approach minimizes the overall risk of bias and data-driven results.

## Data Availability

Not applicable.

## Abbreviations

AE: Adverse events
AIS: Acute ischemic stroke
BI: Barthel Index
CRF: Case report form
IDSMB: Intendent Data Safety Monitoring Board
IQCODE: Informant Questionnaire on Cognitive Decline in the Elderly
mITT: modified intention-to-treat
MMP-9: Matrix metalloproteinase-9
mRS: modified Rankin Scale
PH: Parenchymal hemorrhagic transformation
rtPA: recombinant tissue plasminogen activator
SUR1: Sulfonylurea receptor 1
SUSAR: Suspected unexpected serious adverse reaction
TRPM4: Transient receptor potential M4
